### Inclusion and Exclusion Criteria

The inclusion criteria for this study will be as follows: (1) the individual has lived locally for more than 5 years; (2) female participants will ve aged between 45 and 80 years old (45 ≤ age < 80) and male participants will be aged 50 to 80 years old (50 ≤ age < 80); (3) a written informed consent form will be signed by the subjects, and the process of obtaining this informed consent will be ethical. Participants who suffer from mental illness, such as a mental deficiency, memory or thinking disorder, and who are unable to cooperate with investigators due to disability or lack of physical capacity will be excluded.

### Bone Density Screening

A dual-energy X-ray absorptiometry (DEXA) device (HOLOGIC Wi, United States) will be used to detect the lumbar spine and bilateral hips and to record the *T* and *Z*-values of each site. The precision of the instrument will be set at 1%, that is, the error of repeated measurement will be <1%. After using the instrument every day, professional staff will be responsible for checking accuracy and maintenance.

### Biochemical Indicators of Bone Metabolism Testing

The bone metabolism indicators we will measure will include blood calcium, phosphorus, magnesium, creatinine, alkaline phosphatase, thyroid stimulating hormones, 25-hydroxyvitamin D3, and osteocalcin. Additionally, bone turnover markers, including procollagen type 1 N-terminal propeptide (P1NP) and the β cross-linked C-telopeptide of type 1 collagen (β-CTX), will be determined by electrochemiluminescence.

For each subject, 7 ml peripheral venous blood will be collected in fasting conditions between 8 a.m. and 9 a.m. on the day of physical examination. The anticoagulant vacuum blood collection tube will be 1 ml and the two procoagulant vacuum blood collection tubes will be 3 ml. The Guangzhou KingMed Diagnostics Limited Liability Company is responsible for collecting and testing blood samples.

### Collecting Clinical Information

All participants will complete a face-to-face paper version of the questionnaire and undergo a comprehensive physical examination. The questionnaire and examination will mainly assess the general characteristics of participants, menstrual status, menopausal age, number of pregnancies, number of births, education level, income level, history of smoking and drinking, history of previous illness and medication, number of falls, daily dietary habits, TCM syndrome, and so on. Information on various fractures, such as the number, cause, location, and therapeutic method, will be recorded in detail. The questionnaire will also include the International Physical Activity Questionnaire (21), the 1 Min Osteoporosis Risk Assessment Test of the International Osteoporosis Foundation (22), and the EuroQol 5-dimension instrument (23) to evaluate the physical activity and quality of life of participants.

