This prospective study will investigate conventional risk factors and relevant symptoms as reported in traditional Chinese medicine (TCM) in populations with a high risk of postmenopausal osteoporosis (18, 19). Based on the findings of this preliminary study, we will then conduct a further cross-sectional survey and a prospective follow-up study in the Beijing community. The present prospective study aims to investigate the prevalence of OP and the incidence of osteoporotic fracture in Beijing community residents to further explore the risk factors related to this condition and to put forward some rational suggestions for patients. This research on “Beijing community-based Osteoporosis and osteoporotic fracture screening: a cross-sectional and prospective study (beyond)” will provide reliable data for the prevention of OP and osteoporotic fractures among community-dwellers in the Beijing area.

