## Materials and Methods

This is a community-based cross-sectional and prospective follow-up study. Based on the different economic conditions in Beijing, we will seek residents from several districts from people who respond to an invitation to participate. Then, the participants will be screened, based on predetermined inclusion and exclusion criteria, and an epidemiological investigation will be conducted. The investigation will gather data on BMD screening, biological samples, and questionnaire information. Each participant will be followed for at least 2 years to track incidences of osteoporotic fracture. Based on a power analysis, the required sample size will be at least 1,500 patients. A flow chart of the research process is shown in Figure 1.

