### Primary Outcomes

This study will be divided into two stages. In the cross-sectional study, our primary outcome was BMD. In the follow-up period, an osteoporotic fracture is the most crucial outcome. Although important information on new fractures will be obtained through the self-reports of participants or interviews during the follow-up, we will immediately re-evaluate and confirm the bone mass of patients with new fracture events based on DEXA. Patients who suffer from fractures will be asked to describe when and why they occurred, their fracture site, and treatment after the fracture.

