## Discussion

OP is characterized by low bone mass and microstructured bone tissue degradation (24). The high mortality and morbidity of osteoporotic fractures make them a serious public health threat (25, 26). The incidence and prevalence of fractures also varies across geographic regions and countries (27–30). Therefore, it is important to develop specific and preventive measures. Additionally, the prevalence of OP and associated fractures in the Beijing community has received little attention. The relatively large sample size of the research allows for a systematic investigation of the risk factors associated with OP via the cross-sectional study, including TCM syndrome differentiation and functional activity, which few community studies have previously investigated. Based on the follow-up of fracture outcome, this research will also dynamically monitor the incidence of osteoporotic fractures and explore the influencing factors of osteoporotic fractures in depth through a comprehensive survey.

This study also has several limitations. First, this study may have limited external validity, as it will only include the participants from some districts in the Beijing area. Second, the final results may be influenced by unequal numbers of gender or age groups in the real-world setting, so the clinical practical value will be lower than that of randomized controlled trials. Third, recall bias may arise from some of the retrospective questions, such as patient history relating to previous illness and medication (31). In summary, more useful information on the prevention and control of OP and associated fractures will be beneficial to improving the management of healthcare in the Beijing community.

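### Current habits will be related to BMD and OP in a sample that includes people already aware of their OP or already fractured, so habits changed afterwards can bias the associations behind the planned suggestions.

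*Protocol article*

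**What the plan says.** Under Materials and Methods of the protocol article, one investigation supplies both exposures and outcome: "The investigation will gather data on BMD screening, biological samples, and questionnaire information". Primary Outcomes fixes the outcome of this stage: "In the cross-sectional study, our primary outcome was BMD". Diagnostic Criteria classes OP by T-score alone and does not separate newly found from long-known disease.

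Collecting Clinical Information lists "history of smoking and drinking, history of previous illness and medication, number of falls, daily dietary habits" among the questionnaire items and adds a physical activity questionnaire. It also expects people with earlier fractures: "Information on various fractures, such as the number, cause, location, and therapeutic method, will be recorded in detail". No reference period is given for diet or activity.

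The only exclusion concerns mental illness and inability to take part: "Participants who suffer from mental illness, such as a mental deficiency, memory or thinking disorder, and who are unable to cooperate with investigators". Known OP, OP treatment and earlier fracture are all admitted.

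The Discussion states that the sample size "allows for a systematic investigation of the risk factors associated with OP via the cross-sectional study". The Introduction intends to "explore the risk factors related to this condition and to put forward some rational suggestions for patients", and the Abstract also plans suggestions for the study's age range. Data Management and Statistical Analysis names age, gender and comorbidities as examples of adjustment factors. The limitations in the Discussion cover external validity, unequal gender and age groups, and recall bias, but not reverse causation.

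**The concern.** A person told of OP, or treated for a fracture, may change diet or alcohol use, and may exercise more on advice or move less after injury. If the questionnaire records the changed habit, the habit is partly a result of the outcome it is meant to explain. This differs from recall bias, because a perfectly reported current habit is still affected. It also differs from drug treatment altering the T-score, because here the exposure moves and BMD need not.

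Age, gender and comorbidities do not identify who changed behaviour after a diagnosis, so adjusting for them leaves the problem in place. It falls on the modifiable factors, which are the ones that advice to residents would draw on. A habit taken up after diagnosis would look harmful, and a habit given up would look protective.

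The problem belongs to the cross-sectional analysis of BMD and OP. For new fractures during follow-up, baseline habits precede the outcome, although behaviour changed by earlier OP or fracture can still confound that analysis.

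**Working it through.** The plan gives no figure for this point, so there is none to reproduce. The article gives no share of OP cases already aware and no habit frequencies. Everything below on those two matters is an assumption, shown as a range.

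**1. Habit with no effect, adopted after diagnosis.** Assume the habit is present in 20% of people. Let k be the share of OP cases already aware (10%, 20%, 30%) and u the habit's frequency among them (40% or 60%). No one in the non-OP group is assumed aware; some awareness there would dilute the bias.

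Exposure among OP cases: p = 0.20(1 − k) + u·k. Observed OR = [p/(1 − p)] / [0.20/0.80].

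| k | u | p | OR (true OR 1) |
|---|---|---|---|
| 10% | 40% | 0.22 | 1.13 |
| 10% | 60% | 0.24 | 1.26 |
| 20% | 40% | 0.24 | 1.26 |
| 20% | 60% | 0.28 | 1.56 |
| 30% | 40% | 0.26 | 1.41 |
| 30% | 60% | 0.32 | 1.88 |

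**2. Habit that is truly protective.** Take an assumed true OR of 0.7. Exposure among cases before any change has odds 0.25 × 0.7 = 0.175, that is 0.175/1.175 = 0.149. Putting 0.149 in place of 0.20 in the formula for p gives these observed ORs:

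| k | u = 40% | u = 60% |
|---|---|---|
| 10% | 0.84 | 0.96 |
| 20% | 0.99 | 1.26 |
| 30% | 1.16 | 1.59 |

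The association crosses to the harmful side in three of the six cells. In the other three it is weakened or lost but not reversed.

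**3. Habit with no effect, given up after diagnosis.** Let b be the habit's frequency and c the fraction of aware, exposed cases who stopped. Exposure among cases is b(1 − kc). The article requires at least 1,500 participants. Its Introduction cites prevalences of 8.08% and 9.65% from another region. Together these imply 1,500 × 0.0808 ≈ 121 to 1,500 × 0.0965 ≈ 145 OP cases. The last column is the normal-approximation probability that a two-sided 5% comparison of proportions is significant in the spurious direction; without bias it would be about 2.5%.

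| k | c | b | Exposure in cases | OR | P(significant) |
|---|---|---|---|---|---|
| 10% | 30% | 30% | 0.291 | 0.96 | 4% |
| 10% | 30% | 50% | 0.485 | 0.94 | 5% |
| 30% | 50% | 30% | 0.255 | 0.80 | 17–19% |
| 30% | 50% | 50% | 0.425 | 0.74 | 35–40% |
| 50% | 50% | 30% | 0.225 | 0.68 | 40–47% |
| 50% | 50% | 50% | 0.375 | 0.60 | 76–82% |

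The bias is thus negligible when few cases are aware and material when a third to a half are aware and many of them change. Its direction depends on whether the habit is adopted or dropped.

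**The case against.** The strongest reply is that this is a limit of every cross-sectional survey, and that an article may leave the choice of analysis set to a fuller plan. The adjustment list is open-ended, and the illness, medication and fracture histories needed to deal with the problem are already to be collected. That stands in part: the article does not fix a faulty analysis set. What it does state is the combination of open eligibility, exposure and outcome gathered together, risk factors drawn from that stage, and suggestions as the product. That combination creates the risk, and its limitations do not mention it.

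The Introduction also says that OP in the community is typically undiagnosed until a fracture occurs, which points to low awareness and small bias. This is a fair point on size. It does not settle it, because people who have already fractured are admitted.

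Four stronger readings are tempting but not supported:

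- A reader might infer that habits are recorded as they stand on the day of the scan. Same-day timing is not stated, and smoking and drinking are asked as a history, which may capture past use. The concern applies to those two only where current use is recorded. The illness, medication and falls items are not habits.
- A reader might infer that the plan will report these factors as causes. The article speaks of association and correlation. What presumes a direction is the step from association to suggestions.
- A reader might infer that protective habits will come out as harmful. The second calculation shows that only for part of the assumed range.
- A reader might infer that unaware participants should form the main analysis. That would drop many of the more severe cases and would set OP against no OP ahead of the stated primary outcome, BMD.

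**Conclusion.** The concern holds in limited form. As written, the plan allows habits changed after a diagnosis or fracture to bias the cross-sectional associations of modifiable factors with BMD and OP, in either direction, and the named adjustment factors do not correct this. The size cannot be determined from the article. For a habit with no effect, the illustrative ORs run from 1.13 to 1.88 if 10% to 30% of cases are aware and the habit is two to three times as common among them. If the habit is instead dropped, they run from 0.96 down to 0.60 as awareness rises from 10% to 50%. These figures rest wholly on assumed awareness, habit frequency and behaviour change, and on no awareness in the non-OP group. The change is worth making because suggestions are planned and the data needed are largely being collected. Prevalence estimates are not affected.

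**What to change.** For modifiable factors (diet, physical activity, and smoking and drinking where current use is recorded), pre-specify an analysis of BMD and of OP against no OP, restricted to participants with no earlier OP diagnosis, no OP medication and no earlier low-trauma fracture. Report it beside the all-participant analysis, not in place of it. Identify these participants from the illness, medication and fracture histories in Collecting Clinical Information, after confirming that the form records an earlier OP diagnosis explicitly, since the article mentions only previous illness in general.

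Base lifestyle suggestions only on factors whose direction holds in the restricted group. Add reverse causation to the limitations in the Discussion. Keep all participants for prevalence.

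The cost is analysis wording, one further table and, if the form lacks it, one question on earlier diagnosis. The restricted analysis will have fewer and milder OP cases. At 10% to 30% awareness, the 121 to 145 cases would fall to between 121 × 0.7 ≈ 85 and 145 × 0.9 ≈ 130, before any further loss for earlier fracture. Because the cases dominate the variance, intervals would widen by a factor of roughly 1/√0.9 to 1/√0.7, about 5% to 20%.

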### Follow-up Study

A subsequent follow-up study will be conducted annually until December 2020.

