## Abstract

**Background:** Osteoporosis (OP) patients are usually asymptomatic until osteoporotic fractures occur, which makes early diagnosis and prevention difficult, and the associated fractures secondary to OP could be preventable with appropriate management. Therefore, early identification and relevant evidence-based management of OP could guide the prevention of subsequent fractures. This study will investigate the prevalence of OP and the incidence of osteoporotic fractures in Beijing community residents to further explore the related risk factors and put forward suggestions for people aged 45–80 years old.

**Methods:** Over 2 years, this study will conduct an OP screening and a prospective follow-up in the Beijing community to investigate the incidence of osteoporotic fractures. The study will undertake bone mineral density detection, collect biological samples, and record information via questionnaires.

**Discussion:** The study aims to investigate the potential risk factors for osteoporosis and explore syndromes from traditional Chinese medicine that are associated with this condition based on large samples from the Beijing community. Data on the incidence of osteoporotic fractures among community dwellers in Beijing over the two-years will be available on the Chinese clinical trial registry: ChiCTR-SOC-17013090.

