### Data Management and Statistical Analysis

Data will be recorded in the case report form (CRF), and it will be reviewed and validated by researchers, data managers, and statisticians for final statistical analysis at the end of this study. The CRF will be entered into Epidata 3.1 software by two researchers independently, and the recorded data will be checked for consistency. If there are inconsistencies, the CRF or other original records will be carefully verified. The data will be modified one by one until the independently entered data are identical. The data administrator will further check the exported database and use a logic check to check data until and doubts are resolved. The electronic database will eventually be locked.

IBM SPSS version 22.0 (SPSS, Chicago, IL, United States) software will be used to analyze the data. Continuous data will be analyzed using the independent *t*-test or Wilcoxon's rank sum test, while categorical data will be compared using the chi-square or Fisher's exact test. All statistical analysis tests will be performed using a two-sided hypothesis test. The *P* ≤ 0.05, and the difference in the test will be considered statistically significant. We will also adjust the correlation analyses for factors such as age, gender, and comorbidities.

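### The follow-up period for fracture is stated inconsistently, and a calendar end date with no stated enrolment close leaves exposure unequal, so a crude proportion read as 2-year incidence may be biased in either direction

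*Protocol article*

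**What the plan says.** Three places in the Protocol article define how long people are followed.

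- Abstract, Methods paragraph: "Over 2 years, this study will conduct an OP screening and a prospective follow-up in the Beijing community". The Abstract's Discussion paragraph then names the quantity to be made available: "Data on the incidence of osteoporotic fractures among community dwellers in Beijing over the two-years".
- Materials and Methods, opening paragraph: "Each participant will be followed for at least 2 years to track incidences of osteoporotic fracture".
- Follow-up Study, whose entire text is: "A subsequent follow-up study will be conducted annually until December 2020".

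Primary Outcomes makes osteoporotic fracture the key outcome of the follow-up stage, and has patients say when a fracture occurred. Participant Recruitment describes posted advertisements in 2 to 5 communities across two districts, with no opening or closing date. Data Management and Statistical Analysis names the t-test or rank sum test for continuous data, chi-square or Fisher's exact test for categorical data, and correlation analyses adjusted for factors such as age. It names no method that uses follow-up time, and does not say how incidence will be estimated.

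**The concern.** Follow-up length is part of the definition of an incidence, and a reader cannot tell from the article which of the three rules governs. An analysis plan cannot settle this later, because it does not decide how long people are contacted.

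A per-person minimum combined with a calendar end also means that time at risk depends on entry date. If fracture is then treated as a yes/no variable, people with different time at risk are counted alike. The proportion obtained is not a 2-year incidence unless exposure happens to be 2 years for everyone. Comparisons between groups would be distorted as well wherever entry date is related to the factor being studied. At stake is the one number that the Abstract promises from the prospective stage.

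**Working it through.** There is no stated figure to reproduce on this point. The only design figure is a sample size of at least 1,500, and the argument does not depend on it.

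**Step 1: compare the statements in pairs.**

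- *Abstract against Materials and Methods.* If screening and follow-up together take 24 months and enrolment lasts *r* months, follow-up ranges from 24 − *r* to 24 months. A minimum of 24 months for each person then needs *r* = 0, that is, everyone screened at once. For at least 1,500 people recruited by advertisement this is not realistic, so the two conflict on a plain reading.
- *Materials and Methods against Follow-up Study.* December 2020 minus 2 years is December 2018. Both hold if the last entry is by then. The article neither requires nor excludes this.
- *Abstract against Follow-up Study.* No conflict in themselves, since a 2-year study could end in December 2020.

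**Step 2: exposure by entry date.** Available follow-up is December 2020 minus the entry date. Entry after December 2018 gives under 24 months, and entry before it gives over 24 months.

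**Step 3: effect on a crude proportion.** These are illustrations only, because the enrolment windows are assumptions. Assume uniform entry from January 2018, a constant low fracture hazard and no losses. The crude proportion divided by the true 2-year risk is then approximately mean follow-up in months / 24. Two ways of counting are possible, and the article specifies neither:

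- (a) only fractures within 24 months of entry count, but people with less than 24 months stay in the denominator;
- (b) every fracture up to December 2020 counts.

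| Assumed enrolment close | Short of 24 months | Mean under (a) | Ratio (a) | Range and mean under (b) | Ratio (b) |
|---|---|---|---|---|---|
| December 2018 | 0% | 24 | 24/24 = 1.00 | 24 to 36, mean 30 | 30/24 = 1.25 |
| June 2019 | 6/18 = 33% | 24 − (6/18) × 3 = 23 | 23/24 = 0.96 | 18 to 36, mean 27 | 27/24 = 1.125 |
| December 2019 | 12/24 = 50% | 24 − (12/24) × 6 = 21 | 21/24 = 0.875 | 12 to 36, mean 24 | 24/24 = 1.00 |

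Exact calculation with 1 − exp(−rate × time), at assumed hazards of 0.5%, 1% and 2% per year, gives nearly the same ratios: 0.96 and 0.88 under (a) for the last two rows, and 1.24 to 1.25, 1.12 and 1.00 under (b).

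The sign therefore depends on both the enrolment dates and the counting rule. Under (b), even an enrolment close that honours the 2-year promise overstates 2-year incidence.

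**Step 4: estimators that use time.** Kaplan-Meier and person-time estimates are not biased by administrative censoring alone. The distortion in Step 3 belongs to the crude proportion only.

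**The case against.** The strongest reply is that this is loose wording in a condensed article. "Over 2 years, this study will conduct an OP screening and a prospective follow-up" may simply mean a 2-year follow-up, and the Abstract's later reference to incidence over two years supports that. The other two statements fit together once enrolment closes by December 2018. The ethics and registry numbers point to 2017, which would leave time for it. Recruitment dates and the incidence estimator commonly sit in the full protocol or analysis plan, neither of which is shown. Fracture dates are to be collected, so a proper time-based analysis is possible.

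Much of this stands. The missing enrolment dates and estimator are not faults in themselves. A reader might infer more than the text supports:

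- That all three statements are mutually incompatible. They are not; only the Abstract and Materials and Methods conflict on a plain reading.
- That late entrants cannot reach 2 years. This is true only of entry after December 2018, and the article does not say that anyone enters then.
- That 2-year incidence is understated. This needs late entry, a crude proportion and exclusion of fractures after 24 months. Counting all follow-up gives an overstatement or no net bias under the same enrolment windows.
- That the community recruited last bears most of the bias. Nothing says that communities are recruited in sequence.

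What the reply does not remove is that the article itself gives the follow-up length in statements that do not fit together, and that its fixed end date does not by itself secure the 2-year minimum it promises.

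**Conclusion.** The point holds in a limited form. The Abstract and Materials and Methods conflict on a plain reading, and the December 2020 end delivers the per-person minimum only under an enrolment close that the article does not state. Exposure will differ between participants whenever entry is staggered. A crude proportion read as 2-year incidence may then be biased in either direction.

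The size cannot be fixed from the document. The ratios of about 0.875 to 1.25 show only what assumed enrolment windows and two counting rules would produce. They also assume uniform entry, a constant low hazard and no losses. If the analysis uses follow-up time, administrative censoring alone causes no bias and only the inconsistency in wording remains. This is worth correcting, but it does not invalidate the design.

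**What to change.** 1. Use one definition of follow-up in the Abstract, Materials and Methods and Follow-up Study. Either close enrolment by 31 December 2018 with follow-up to 31 December 2020 (the article gives no day, so state it), or replace the calendar end with each participant's second anniversary. If enrolment has already closed, give the actual dates.
2. Correct the Abstract so that 2 years describes follow-up per person, not screening and follow-up combined.
3. Report 2-year incidence from each participant's own baseline date. Censor anyone with less than 2 years at last contact, using Kaplan-Meier or a person-time rate, and show fractures after 2 years separately. Compare groups with a method that uses follow-up time, keeping chi-square or Fisher's test for outcomes where exposure is equal.

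The cost is wording, slightly more analysis work using fracture dates that are already to be collected, and possibly some further annual contacts if late entrants are followed to their second anniversary.
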